### Drop-outs

All families who consented to participate in the study will be followed from pretest to the follow-up assessment eight months later. If families drop out of the intervention, a post-test and follow-up assessment will still be planned if possible. If, for some reason, the assessments cannot take place the principle of last value carried forward will be applied. The reasons for drop-out will be documented and analyzed and the involved organization will be notified of these reasons in order to use this information to possibly improve the implementation of the intervention. Intention-to-treat analyses will be conducted to account for drop-out.

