### Sample size calculation

The total sample size is based on an expected effect size of *d* = 0.33 (*f* = 0.17), based on a meta-analysis on RCTs of interventions focusing on improving maternal sensitivity [15]. Based on an alpha of 0.05 and a sample of 100 families, adequate statistical power will be achieved (0.97) for testing the significance of an interaction effect between the between-subject factor (experimental versus control condition) and the within-subject factor (assessment: pretest, post-test, follow-up) in repeated measures analysis of variance (ANOVA) using the full sample of 100 families. If, due to circumstances such as drop-out, illness of VIPP-V intervention workers or unexpected organizational aspects, the number of families drops, with an effect size this high, high power (0.80) can still be achieved with 58 families for the main research question regarding effectiveness of intervention on parental sensitivity. However, to also perform moderator analyses with adequate power we aim to include 100 families in the study.

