### Data analysis

All analyses will be done using the software program SPSS (version 21.0). Baseline characteristics will be described in descriptive analyses. Before analyzing, differences in baseline characteristics between the experimental and control condition will be checked. If differences are found, they will be reported and controlled for in further analyses. Before analyzing, outliers will be checked and winsorized if necessary. For analyses of the primary and secondary outcome measures of the study (parental sensitivity, parent-child interaction quality, parental self-efficacy and parenting stress) ANOVA repeated measures or multilevel analyses will be used, depending on the level of clustering in the data. Intention-to-treat and completer analyses will be performed. The primary and secondary outcome measures of families in the experimental condition will be compared with their own scores on a previous assessment, as well as with scores of families in the control condition at the same assessment. Change over time from pretest to post-test and from pretest to follow-up in parental sensitivity, quality of parent-child interaction, parental self-efficacy and parenting stress will be assessed in the experimental group, and compared with the control group. Results will be described as rates of change. The outcome measure regarding feasibility of the intervention ‘Experiences of VIPP-V intervention workers with VIPP-V during early intervention’ will be reported in descriptive analyses. Multivariate regression analysis or multilevel moderator analyses will be performed with different predictors (demographic variables, child’s developmental age, working alliance between parent and VIPP-V intervention worker, empathy of the VIPP-V intervention worker) to study for whom and under which circumstances VIPP-V intervention is most effective. For these analyses only the data of the families in the VIPP-V intervention condition will be used.

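### Last value carried forward for missed assessments can bias the intention-to-treat comparison of change and misstate its precision

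*Protocol article*

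**What the plan says.** The Drop-outs section of the protocol article takes three steps. It first limits missing data: "If families drop out of the intervention, a post-test and follow-up assessment will still be planned if possible". For any assessment that still cannot be held it fixes one method, without exception: "the principle of last value carried forward will be applied". It then relies on the analysis set: "Intention-to-treat analyses will be conducted to account for drop-out".

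The Data analysis section makes change from baseline the quantity of interest: "Change over time from pretest to post-test and from pretest to follow-up in parental sensitivity", and likewise for the other outcomes, is assessed in the VIPP-V arm and compared with control. Two analysis sets are named: "Intention-to-treat and completer analyses will be performed". On the model: "ANOVA repeated measures or multilevel analyses will be used, depending on the level of clustering in the data". The choice of model therefore turns on clustering and not on missing data.

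**The concern.** Carrying a value forward asserts that the dyad stayed where it was last seen. If pretest is carried, both change scores are exactly zero. If post-test is carried, the change between post-test and follow-up is zero, which amounts to full maintenance of whatever had been reached. Change from pretest, compared between arms, is what the trial estimates, so the rule writes an assumed answer into the outcome itself.

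Two things are at stake. The intention-to-treat contrast comes to depend on how many families in each arm miss assessments. And the analysis counts constructed values as measured ones, so standard errors and tests do not reflect the information collected.

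Nothing else in the article removes the problem. The completer analysis omits the same families. If clustering leads to the multilevel option, the carry-forward sentence still applies as written, and the model would be fitted to filled-in data.

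**Working it through.** **Inputs from the article.** Effect d = 0.33 (f = 0.17), alpha 0.05 and 100 families (Sample size calculation); 1:1 allocation and three assessments (Study design); eight months from pretest to follow-up (Drop-outs).

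**Inputs assumed.** The article gives no rate of missed assessments and no expected control-arm change. I use losses of 10% to 30% per arm and control-arm changes of -0.2 to 0.4 SD.

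**The plan's own figure.** For the group-by-time interaction, the noncentrality is λ = f²·N·m/(1−ρ) with m = 3. Sphericity and ρ = 0.5 are assumed, because the article states neither.
- N = 100: λ = 0.0289 × 100 × 3 / 0.5 = 17.34, df 2 and 196, power 0.967 (stated 0.97).
- N = 58: λ = 0.0289 × 58 × 3 / 0.5 = 10.06, df 2 and 112, power 0.807 (stated 0.80).

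The power statement reproduces and is not in dispute. The planned 0.33 serves below as the true effect.

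**Expected carry-forward estimate at post-test.** Let D be the true effect, c the control-arm change, and pE and pC the shares lost before post-test on VIPP-V and control. Lost families are assumed to have the same true change as the others in their arm. Each contributes a change of zero, so

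E = (1−pE)(c + D) − (1−pC)c = D − pE·D + (pC − pE)·c.

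The second term is attenuation. The third is an error that exists even when D = 0, and it takes its sign from which arm loses more and from the direction of c.

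| D | c | pE / pC | Calculation | E | Bias |
|---|---|---|---|---|---|
| 0.33 | any | 10% / 10% | 0.9 × 0.33 | 0.297 | −0.033 |
| 0.33 | any | 20% / 20% | 0.8 × 0.33 | 0.264 | −0.066 |
| 0.33 | 0 | 30% / 10% | 0.7 × 0.33 | 0.231 | −0.099 |
| 0.33 | 0.4 | 20% / 10% | 0.8 × 0.73 − 0.9 × 0.4 | 0.224 | −0.106 |
| 0.33 | 0.4 | 30% / 10% | 0.7 × 0.73 − 0.9 × 0.4 | 0.151 | −0.179 |
| 0.33 | 0.4 | 10% / 30% | 0.9 × 0.73 − 0.7 × 0.4 | 0.377 | +0.047 |
| 0 | 0.4 | 30% / 10% | 0.7 × 0.4 − 0.9 × 0.4 | −0.08 | −0.08 |
| 0 | 0.4 | 10% / 30% | 0.9 × 0.4 − 0.7 × 0.4 | +0.08 | +0.08 |

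**Check by simulation.** 50 families per arm, correlation 0.5, 4,000 runs per setting, baseline-adjusted comparison at post-test, loss unrelated to outcome.
- D = 0.33, c = 0, 20% lost in each arm: 0.264 with carry-forward, 0.330 from observed data.
- D = 0, c = 0.4, 10% / 30% lost: estimate 0.074 and type I error 0.073 with carry-forward; −0.005 and 0.053 from observed data.
- D = 0, c = 0.4, 30% / 10% lost: −0.084 and 0.086 with carry-forward; −0.004 and 0.052 from observed data.

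**Loss after post-test.** The post-test contrast is untouched. The follow-up contrast is off by whatever these families would have gained or lost in the last three months. The article offers no basis for sizing that, so I give no figure.

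**The case against.** **Continued assessment.** Leaving the intervention is not the same as having missing data, because the article plans to assess those families anyway. A reader might infer that every dropout is scored as unchanged. The text does not support that: the rule covers only assessments that cannot be held, and a family lost after post-test keeps its post-test score. This limits how often the rule is used, not what it does when used.

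**No documented drift or unequal loss.** This stands. The article does not show that parental sensitivity rises over eight months, and the 0.4 SD used above exceeds the planned effect. With c = 0 the spurious term vanishes and only attenuation is left. What the article does offer is plausibility: it hypothesises a stronger improvement than under usual care, usual care includes parenting guidance, only one arm receives seven home visits, and families learn their condition before pretest.

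**Families who stop may truly have gained nothing from VIPP-V.** Then the effect over all randomised families is (1−pE)D, and with equal loss carry-forward returns exactly that. With unequal loss an error of (pC − pE)c remains: at 30% / 10% and c = 0.4 the target is 0.231 and the rule gives 0.151. So the rule cannot be defended as reliably conservative.

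**A second analysis is planned.** Completer results will stand beside the intention-to-treat results, and the article does not say which is primary. But the completer set is valid only if loss is unrelated to outcome given what is adjusted for.

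**Two stronger readings that the article does not support.** One might read the figure of 58 families as an expected 42% loss of outcomes. It is the number at which power is still 0.80, computed on 58 families, and not a forecast of missing data. One might also hold against the rule that a family lost between randomisation and pretest has nothing to carry. A mixed model gains no outcome information from such a family either, unless it is assessed later.

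**Conclusion.** The concern holds for missed assessments. The article fixes a single-value imputation that sets the analysed change to zero for families unseen after pretest and assumes no further change for those lost after post-test. This can bias the intention-to-treat estimate and misstate its precision, and neither the completer analysis nor the conditional multilevel option repairs it.

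Under equal loss the effect shrinks in proportion: by a tenth at 10% and a fifth at 20%. Under unequal loss of 10% to 30% per arm and control-arm change between -0.2 and 0.4 SD, the bias on a true 0.33 runs from about −0.18 to +0.05 SD. With no true effect and c = 0.4 it reaches ±0.08 SD. These sizes rest on assumed loss rates and control-arm change, on all loss falling before post-test, and on lost families having the same true change as the others. They show what the rule can do; they do not predict this trial's result. If few assessments are missed, the effect will be small.

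**What to change.** Replace the carry-forward sentence in the Drop-outs section with wording to this effect:

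*The intention-to-treat analysis uses every observed T1, T2 and T3 value of all randomised families in a likelihood-based mixed (multilevel) model, or multiple imputation by arm, assuming data are missing at random. This applies whatever the level of clustering. Last value carried forward is used, if at all, only as a sensitivity analysis.*

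Align the Data analysis section, so that clustering decides which random effects are needed and no longer whether a mixed model is used. Keep the commitment to assess families who leave the intervention, since it does most to limit the problem.

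The cost is a change of wording and of analysis syntax. Multilevel analysis is already named, the stated software can fit such a model, and no extra data are needed. The Status of the trial section reports data collection as still in progress, so the change can be made and dated before outcomes are analysed by arm.

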### Data analysis

All analyses will be done using the software program SPSS (version 21.0). Baseline characteristics will be described in descriptive analyses. Before analyzing, differences in baseline characteristics between the experimental and control condition will be checked. If differences are found, they will be reported and controlled for in further analyses. Before analyzing, outliers will be checked and winsorized if necessary. For analyses of the primary and secondary outcome measures of the study (parental sensitivity, parent-child interaction quality, parental self-efficacy and parenting stress) ANOVA repeated measures or multilevel analyses will be used, depending on the level of clustering in the data. Intention-to-treat and completer analyses will be performed. The primary and secondary outcome measures of families in the experimental condition will be compared with their own scores on a previous assessment, as well as with scores of families in the control condition at the same assessment. Change over time from pretest to post-test and from pretest to follow-up in parental sensitivity, quality of parent-child interaction, parental self-efficacy and parenting stress will be assessed in the experimental group, and compared with the control group. Results will be described as rates of change. The outcome measure regarding feasibility of the intervention ‘Experiences of VIPP-V intervention workers with VIPP-V during early intervention’ will be reported in descriptive analyses. Multivariate regression analysis or multilevel moderator analyses will be performed with different predictors (demographic variables, child’s developmental age, working alliance between parent and VIPP-V intervention worker, empathy of the VIPP-V intervention worker) to study for whom and under which circumstances VIPP-V intervention is most effective. For these analyses only the data of the families in the VIPP-V intervention condition will be used.

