#### Care-as-usual

Families randomized into the experimental condition will receive both VIPP-V and care-as-usual, while families randomized into the control condition will receive only care-as-usual. At Royal Dutch Visio and Bartiméus families receive care for a wide range of issues and topics, such as mobility training and magnifier training for the child, and guidance for parents on parenting issues, play behavior and choice of schools. At pretest, post-test and follow-up all families are asked about the kind and amount of care they have received recently. An analysis and comparison will be made of the received care-as-usual in both conditions. If necessary, kind and amount of care-as-usual will be controlled for in analyses.

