### Randomization

Randomization will be done by use of a computerized random number generator by the first author. Using stratified randomization, equal randomization of families from both Royal Dutch Visio and Bartiméus will be achieved, as well as equal representation of children with varying chronological ages. Stratified randomization reduces the risk for baseline imbalance between conditions [44]. For each organization separately, the random allocation list will be generated in three blocks with a 1:1 allocation, based on three periods in which the intervention will be offered. After the second block a check will be done for baseline imbalances between conditions, so, if necessary, these imbalances can be corrected in the final block. Each block will be randomized roughly three weeks before the start of the intervention. The numbers on the list will be paired with the participating families in order of the date on which informed consent is obtained.

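### Covariates are picked by checking for baseline differences, and T1 is used only as a repeated outcome or in change scores; one fixed T1-adjusted model would be more precise

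*Protocol article*

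**What the plan says.** **Covariates.** Data analysis: "Before analyzing, differences in baseline characteristics between the experimental and control condition will be checked". It continues: "If differences are found, they will be reported and controlled for in further analyses". No variable, test or threshold is named. Care-as-usual has a second conditional rule, for a variable that arises after randomisation: "If necessary, kind and amount of care-as-usual will be controlled for in analyses".

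**Model.** Data analysis: "ANOVA repeated measures or multilevel analyses will be used, depending on the level of clustering in the data".

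**Role of T1.** The power statement in Sample size calculation is for "testing the significance of an interaction effect between the between-subject factor" (condition) and "the within-subject factor (assessment: pretest, post-test, follow-up) in repeated measures analysis of variance (ANOVA"). T1 is thus one of three outcome levels. Data analysis adds three further comparisons: families in the VIPP-V arm against their own previous scores; the same families "as well as with scores of families in the control condition at the same assessment"; and change from T1 to T2 and from T1 to T3, compared between arms. None of these is described with T1 as a covariate.

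**Design factors.** Randomization describes stratification by organisation and child's chronological age, with three blocks per organisation tied to intervention periods. The reason given is: "Stratified randomization reduces the risk for baseline imbalance between conditions". The article does not list the terms of the outcome model.

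**Timing of T1.** Under Procedure and Blinding, families are told their condition directly after their block is randomised, and the T1 visit is arranged after that.

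**The concern.** The check-then-adjust rule is written into the plan, so it is not a detail left to a later document. In a randomised comparison, most baseline differences between arms reflect the luck of the draw. A difference between arms says nothing about whether a variable predicts the outcome, and adjusting for a non-predictive variable buys no precision. A strongly prognostic variable that happens to be balanced would be left out, although including it would sharpen the estimate. The final model also cannot be known until the data are seen, because it depends on which checks are judged positive.

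Meanwhile the strongest predictor likely to be available, the T1 score of the same outcome, is already collected but enters only as a repeated outcome or through a difference. With 100 families, the precision given up matters.

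**Working it through.** **1. The plan's own power figure.** Inputs from Sample size calculation: f = 0.17, alpha 0.05, N = 100 (fallback 58), 2 groups, 3 assessments. No within-person correlation (rho) is given; assume 0.5. Noncentral F with λ = f²·N·3/(1 − rho):

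- N = 100: λ = 0.0289 × 300 / 0.5 = 17.34, df 2 and 196, power 0.967 (stated 0.97).
- N = 58: λ = 0.0289 × 174 / 0.5 = 10.06, df 2 and 112, power 0.807 (stated 0.80).

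Both reproduce, so no arithmetic error is at issue. The powers below are lower because they take d = 0.33 as the difference between arms at a post-baseline visit, with none at T1. With that difference at both T2 and T3, the interaction has λ = 100 × (0.33²/4) × (2/3) / 0.5 = 3.63 and power 0.38, whereas the plan enters f = 0.17 directly as the interaction effect.

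**2. Change score against T1 as covariate, same contrast.** Assume SD 1 at each visit, compound symmetry, 50 per arm, two-sided 0.05. The noncentrality is (0.33 / SD factor) × √(100/4).

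- Change score: SD factor √(2(1 − rho)).
- T1 as covariate: SD factor √(1 − rho²).
- Variance ratio, covariate to change: (1 − rho²) / (2(1 − rho)) = (1 + rho)/2.

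Example at rho = 0.5: change 0.33/1.000 × 5 = 1.65, power 0.37; covariate 0.33/0.866 × 5 = 1.91, power 0.47.

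| T1-to-T2 contrast | rho 0.3 | rho 0.5 | rho 0.7 |
|---|---|---|---|
| Power, change score | 0.28 | 0.37 | 0.56 |
| Power, T1 as covariate | 0.40 | 0.47 | 0.63 |
| Variance ratio | 0.65 | 0.75 | 0.85 |
| Total N for 80% power, change | 404 | 290 | 174 |
| Total N for 80% power, covariate | 264 | 218 | 148 |

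The unadjusted comparison at T2 alone has power 0.37 whatever rho is. At rho 0.8 the variance ratio is 0.90, so the gain shrinks as rho rises.

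**3. The same comparison for the mean of T2 and T3.** Variance by change is (1 + rho)/2 + 1 − 2rho; with T1 as covariate it is (1 + rho)/2 − rho². Power by change is 0.36, 0.47 and 0.68; with T1 as covariate it is 0.59, 0.64 and 0.78 (rho 0.3, 0.5, 0.7).

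**4. How often the rule fires by chance.** Assuming independent checks at the 5% level (the article gives no level), the chance of at least one positive is 1 − 0.95^k: 0.34 for k = 8 and 0.51 for k = 14. Fourteen is the number of items in the demographic questionnaire.

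**5. What the rule does to error rates.** Simulation: N = 100, 8 candidate covariates with joint correlation 0.4 with the outcome, checks at 5%, 6000 runs per setting.

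| | rho 0.5 | rho 0.7 |
|---|---|---|
| Type I error, check-then-adjust | 0.046 | 0.041 |
| Type I error, better of adjusted and unadjusted | 0.055 | 0.053 |
| Power, change score, no adjustment | 0.367 | 0.564 |
| Power, change score, check-then-adjust | 0.359 | 0.561 |
| Power, T1 as fixed covariate | 0.470 | 0.630 |

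The gain from adding organisation, period and age cannot be computed, because the article gives no correlation of these with the outcomes.

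**The case against.** The best defence is that nothing here is invalid. Repeated-measures and change-score analyses are legitimate in a randomised trial, and the planned between-arm change comparison already uses T1. Adjusting for T1 is a gain in efficiency, not the correction of an error. That stands, and it limits the point to precision and a fixed model.

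The second objection concerns T1 itself. It is collected after families know their condition, by unblinded assistants, so a T1 difference may partly reflect disclosure. The planned correction of imbalances in the final block is a further reason not to call every baseline difference pure chance. This stands as a limitation of the remedy, most of all for self-reported self-efficacy and stress; the observed measures are at least coded blind. It does not favour the current plan, because the interaction and change scores rest on the same T1 score, with full weight.

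Stronger readings that a reader might infer, and why the article does not support them:

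- *T1 adjustment lifts power from 0.38 to 0.64, or cuts the detectable d from 0.54 to 0.40 (rho 0.5).* Those pairs also replace a 2-df interaction by a 1-df average of T2 and T3. For the averaged contrast alone, power moves from 0.47 to 0.64 and detectable d from about 0.49 to 0.40.
- *The T2/T3 average should be the main test.* It favours a sustained effect and could hide fading; the article plans the two visits separately.
- *The error term does not match the design.* The article does not list model terms, and a condensed article may leave the stratification factors to the full plan.
- *The rule inflates type I error.* The simulation shows slight conservatism, and little inflation even when the better of two results is reported.

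**Conclusion.** The point holds in a limited form. The written rule chooses covariates largely by chance and leaves the model undetermined until the data are seen; in the simulation it bought no power over no adjustment. The stated tests forgo precision that the T1 score could supply: about 0.12, 0.10 and 0.07 in power for a single contrast at rho 0.3, 0.5 and 0.7. At rho 0.5 this equals a required total of 290 against 218 families for 80% power. These sizes assume d = 0.33 as the difference at the visit, compound symmetry, no attrition and a rho that the article does not give. The direction of the precision gain does not depend on the value of rho below 1.

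**What to change.** Replace the check-then-adjust rule with one model, fixed in advance for each outcome: T2 and T3 scores on condition, visit, condition-by-visit, T1 score, T1-by-visit, organisation, intervention period/block and child's chronological age. Report the condition effect at T2 and at T3 separately, in line with the changes to post-test and follow-up that the article already plans. Present baseline characteristics descriptively, with no role in choosing covariates. Treat every other adjustment, including care-as-usual received, as a sensitivity analysis.

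State as a limitation that T1 is collected after allocation is disclosed, noting that this matters most for the self-reported outcomes, and add a sensitivity analysis without T1 adjustment.

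The covariates are already collected. The cost is a few degrees of freedom, revised analysis wording and a little more analysis work.

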### Hypotheses

The main hypotheses to be tested are:Participation in VIPP-V will be associated with stronger improvement in parental sensitive responsiveness and quality of parent-child interaction than receiving care-as-usual only.Parents participating in VIPP-V will show a stronger increase in parental self-efficacy and a stronger decrease in parenting stress than parents receiving care-as-usual only.

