### Primary outcome measures

The main research question of this study is whether parents of a child with a visual or visual-and-intellectual disability will benefit from participating in VIPP-V in terms of higher parental sensitivity and better parent-child interaction quality compared to receiving care-as-usual only.

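### The analysis section sets an uncontrolled before-after comparison in the VIPP-V arm beside two between-arm comparisons and does not say which one decides effectiveness

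*Protocol article*

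**What the plan says.** The Data analysis section of the protocol article describes three comparisons for every primary and secondary outcome (sensitivity, interaction quality, self-efficacy, parenting stress):

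1. **Within the VIPP-V arm.** Outcomes of these families are set against the same families' earlier scores.
2. **Between arms at one assessment.** The same sentence adds the controls: outcomes "will be compared with their own scores on a previous assessment, as well as with scores of families in the control condition", with both arms taken at matching time points.
3. **Between arms in change.** The next sentence says that change from pretest to post-test and to follow-up "will be assessed in the experimental group, and compared with the control group".

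The section does not rank them. It reserves the word descriptive for baseline characteristics and for the feasibility outcome, and does not apply it to the first comparison.

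Elsewhere the question is comparative throughout:

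- Hypotheses: the first expects "stronger improvement in parental sensitive responsiveness and quality of parent-child interaction than receiving care-as-usual only". The second includes "a stronger decrease in parenting stress than parents receiving care-as-usual only".
- Primary outcome measures: the main research question concerns "higher parental sensitivity and better parent-child interaction quality compared to receiving care-as-usual only".
- Sample size calculation: the stated power is that of "testing the significance of an interaction effect between the between-subject factor (experimental versus control condition) and the within-subject factor", the latter being time of assessment.

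Under Drop-outs, families "will be followed from pretest to the follow-up assessment eight months later". Under Inclusion and exclusion criteria, the children are aged 1 to 5 years. Under Care-as-usual, both arms receive usual services, which include guidance on parenting.

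**The concern.** The first comparison makes no use of the randomised control group. Over eight months a child aged 1 to 5 develops, parent and child gain experience with each other, and usual care continues. Any of these could move the outcomes without VIPP-V, and a before-after test in one arm would pick up all of them together. For self-efficacy and stress, which parents report themselves while knowing their allocation, a within-arm change is harder still to interpret.

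The second comparison is valid under randomisation. As worded, however, it makes no use of the T1 score, which is collected for every one of these outcomes.

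With three comparisons per outcome and no stated order, a report could present a significant rise in the VIPP-V arm as benefit when the difference between arms is null. That matters because the article links a favourable result to broad-scale implementation.

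**Working it through.** **The plan's own figure.** Sample size calculation gives f = 0.17, alpha 0.05, power 0.97 with 100 families and 0.80 with 58. For the condition-by-assessment interaction with 2 groups and m = 3 assessments, the noncentrality is λ = f² · N · m / (1 − ρ), on 2 and 2(N − 2) degrees of freedom. The article does not state ρ. I assumed ρ = 0.5 and sphericity.

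- N = 100: λ = 0.0289 × 300 / 0.5 = 17.34; df 2, 196; power 0.967 (stated 0.97).
- N = 58: λ = 0.0289 × 174 / 0.5 = 10.06; df 2, 112; power 0.807 (stated 0.80).

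Both figures reproduce, so the powered test is the between-arm interaction and not a before-after test.

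**Within-arm test when VIPP-V has no effect.** Inputs: 50 VIPP-V families (Abstract), two-sided alpha 0.05, equal SD at both assessments, a drift of c SD common to both arms, and correlation r between assessments. The values of c and r are assumptions. The standardised mean change is d_z = c / √(2(1 − r)), the noncentrality is d_z · √50, and the critical t on 49 df is 2.01.

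- c = 0.2, r = 0.5: d_z = 0.200, noncentrality 1.414.
- c = 0.2, r = 0.7: d_z = 0.258, noncentrality 1.826.

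| Assumed common drift | P(significant improvement), r = 0.5 | r = 0.7 |
|---|---|---|
| 0 SD | 0.025 | 0.025 |
| 0.1 SD | 0.10 | 0.14 |
| 0.2 SD | 0.28 | 0.43 |
| 0.3 SD | 0.55 | 0.77 |

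For drifts of 0.2 SD or more, counting both tails changes these by 0.001 at most.

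**Between-arm test of change under the same drift.** The expected difference in change is (c + effect) − c = effect. The drift cancels whatever its size, so with no effect the test keeps its 5% level.

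**Precision of the between-arm options at one assessment.** With outcome variance σ² and n = 50 per arm, the variance of the estimated arm difference is:

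- scores at that assessment, unadjusted: 2σ²/n
- change from T1: (2σ²/n) · 2(1 − r)
- adjusted for T1: (2σ²/n) · (1 − r²)

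Against change scores the ratio is (1 − r²) / (2(1 − r)) = (1 + r)/2, a reduction of (1 − r)/2. Against unadjusted scores the reduction is r².

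| r | Unadjusted | Change | T1-adjusted | Cut against change | Cut against unadjusted |
|---|---|---|---|---|---|
| 0.5 | 0.0400σ² | 0.0400σ² | 0.0300σ² | 25% | 25% |
| 0.7 | 0.0400σ² | 0.0240σ² | 0.0204σ² | 15% | 49% |

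**The case against.** The strongest reply is that everything defining effectiveness in the article is comparative: both hypotheses, the main research question, the powered interaction, and the sentence directly after the disputed one. A repeated-measures model routinely yields within-arm and same-time contrasts that help describe an interaction, and the disputed sentence can be read in that way. This stands as far as the main analysis goes. A reader might infer that the trial will count child growth as a treatment effect, but the documents do not support that: no text makes change within the VIPP-V arm a criterion of success, and common drift cancels in the powered test.

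A reader might also suspect regression to the mean. The eligibility criteria rest on disability, age and willingness to take part, with exclusions for developmental age, living situation, parental intellectual disability and siblings. None selects on a low or extreme outcome score, so that argument has no basis here.

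A third tempting reading is that T1 adjustment would save up to 49% of the variance. That holds only against the unadjusted same-assessment comparison. Against the change analysis that is also planned, the saving at r = 0.7 is 15%.

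It is fair to add that the observational primary outcome is rated by coders blind to condition and assessment, and that how far child development moves these ratings is unknown. The role of supporting contrasts may also be settled in a document not shown. None of this removes the point. The article does more than leave the role open: it lists an uncontrolled comparison of all effectiveness outcomes alongside the controlled ones, with no label, in a section that labels other analyses as descriptive.

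**Conclusion.** The point holds as a fault in how the analyses are specified; it does not show bias in the main test. The analysis section names three comparisons per outcome and leaves open which one decides. One of them cannot answer the trial's question, and if read as evidence of benefit it would mislead in about 28% to 43% of trials under no effect and a common drift of 0.2 SD. The range is 10% to 14% at 0.1 SD and 55% to 77% at 0.3 SD. These rates rest on an assumed drift, r between 0.5 and 0.7, equal SDs and all 50 VIPP-V families analysed. They show what an uncontrolled test can do and do not predict what will happen in this trial. The hypotheses and the powered interaction are sound in this respect. The gain in precision from T1 adjustment is a further benefit of the fix; leaving the adjustment out does not make the planned comparison of change invalid.

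**What to change.** In the Data analysis section:

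- State that before-after change is descriptive, and present it for both arms side by side (means and change with confidence intervals at T1, T2 and T3), with no within-arm significance test offered as evidence of effectiveness.
- State that effectiveness is judged only on the between-arm difference at T2 and at T3, each adjusted for the T1 score. This would replace the unadjusted same-assessment comparison.

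The cost is wording only. There are fewer tests, T1 is already collected, and nothing in this point calls for a different sample size. One caution: the stated 0.97 is the power of the interaction test under the assumptions above. It is unaffected by making the before-after comparison descriptive, but it should not be quoted as the power of a T1-adjusted comparison at a single assessment.
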